#### Folic acid fortification and oral clefts

A few countries have introduced folic acid fortification of grain and flour given the strong evidence for a preventive effect of folic acid on neural tube defects (NTDs). Indeed, this evidence and its subsequent application to populations is one of the major public health successes in the field of birth defects (see below). Unlike the case for NTDs, there is no converging evidence for significant changes in birth prevalence for oral clefts post folic acid fortification. In the United States, where folic acid fortification of grain products was mandated on January 1, 1998, three studies have generally found non-significant reductions of 3%
[101], 5%
[102], and 12%
[103] in CL/P prevalence post fortification. A significant 12% reduction in CPO prevalence has been reported
[102].

A slight non-significant increase in the prevalence of oral clefts has been reported after two years of fortification of cereal grain products (1998 through 2000) compared to pre-fortification (1994–1997) period in Ontario, Canada
[104]. Also, in a preliminary evaluation of the effects of fortifying wheat flour with folic acid in Chile starting 2000, Castilla et al.
[105] reported no significant changes in prevalence of oral clefts through the end of 2001 compared to 1999, while significant change of 31% was shown for NTDs. Longer periods may be required for a more comprehensive evaluation of potential changes in prevalence of oral clefts post fortification, yet given the evidence of NTD reduction of up to 50% in similar periods [e.g.
[102,106-108], see Mills and Signore
[109] for a review], these results suggest that low doses of folic acid may be inadequate to even prevent primary occurrence of oral clefts. Further, these studies of prevalence changes over time also suffer from limitations including potential confounding by other simultaneously changing contributory factors and the lack of well-matched control groups.

In Brazil, fortification of wheat and corn flour with folic acid became mandatory in June 2004. Flour is fortified at a dose of 150 μg/100 g, which is lower than that used in Chile (220 μg/100 g of flour) and comparable to the dose used in the United States (average of 150 μg/100 g of cereal grain product). Assuming that women consume about 200 g of fortified flour on average per day, the daily intake of folic acid would be expected to increase by about 300 μg.

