#### Secondary hypotheses

The following secondary hypotheses will be evaluated:

An increase in serum and/or red cell folate levels in all women following daily supplementation with folic acid.

When compared to the 0.4 mg supplemented groups, the 4 mg per day group will have the following:

‐Greater increases in serum and/or red cell folate.

‐Decreases in the recurrence of NSCL/P in each of the following subgroups:

•Women with NSCL/P themselves

•Women with one or more children with NSCL/P

‐A decrease in the severity of NSCL/P in offspring of trial mothers.

‐No increase in twinning rates.

No increase in miscarriage rates.

No increase in rates of preeclampsia.

‐No increase in rates of other birth defects.

‐No decrease in birth weight

‐No decrease in gestational age

A decrease in recurrence of NSCL/P in the group of study subjects compared to an historical control group obtained from the populations served by the craniofacial clinics participating in the study.

A greater decrease in the recurrence of NSCL/P in the group of study subjects receiving 4 mg of folic acid when compared to the historical control group relative to that of the group receiving 0.4 mg when compared to the same control group.

Under separate funding we will examine the role of genes involved in folate metabolism on folate, B12 and homocysteine levels, as well as potential interaction between these genes and the supplementation dose. This project will also establish a resource to examine the long-term outcomes of infants exposed to high dose folic acid in utero.

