#### Historical control group

The recurrence rates in this study will be compared to that of an historical control group. The rationale for using this group relates to the inability to use a placebo control in this study due to ethical considerations. A comparison with an historical control group will allow the assessment of the combined effect of a minimum dose of folic acid of 0.4 mg and a maximum dose of 4 mg by comparing the NSCL/P recurrence rate in the total study group to that of a group of women who did not receive the folic acid dose of 0.4 mg per day. The effect of each of the two folic acid doses on the recurrence risk of NSCL/P could also be evaluated by comparing the NSCL/P rate in each of the two study groups (0.4 mg and 4 mg folic acid) to that of the historical control group.

The historical control will include women with NSCL/P or mothers of children with NSCL/P who are registered at the craniofacial clinics enrolled in the study. Those clinics have been involved in the provision of services to subjects with clefts for an extensive period, thus rates of cleft recurrence can be calculated over an extended time course providing not only cross-sectional data but also trends data adding to the validity of the historical control approach. Such data will reveal any changes in recurrence rates that might have occurred over time.

Taking into consideration the traditional internal validity challenges associated with using historical controls, no major historical events that could affect recurrence rates of NSCL/P in this population are expected to have occurred during the years immediately preceding this study.

Since the two randomized study groups (0.4 mg and 4 mg folic acid) will be compared to the same group of historical controls, any differences in the relative decreases of NSCL/P recurrence rates that may be observed between each of the study groups and the historical control group can be safely attributed to the effect of administered folic acid.

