#### Pilot studies

##### Initial pilot study and subsequent recruitment at Bauru

With funding from NICHD’s Global Network for Women’s and Children’s Health Research, study enrollment was initiated in Bauru in January 2004. This initial pilot aimed at first recruiting about 500 subjects, identified through the records of the Hospital de Reabilitação de Anomalias Craniofaciais (HRAC) clinic, and located within 100 Km of Bauru, using a field-based strategy for recruitment and follow-up. Letters were mailed to 526 women inviting them to enrollment meetings in local communities; 181 women attended the enrollment meetings, and 134 women were enrolled (96% of those eligible). Several factors contributed to low attendance at these enrollment meetings. We found that 23% of the 500 subjects had either moved out of the catchment area or could not be located and that 12% had had a tubal ligation. The inconvenient recruitment and follow up strategies required multiple visits and poor compliance with these was amplified by poverty.

An extension of this pilot study to re-contact potential subjects from the first sample who did not attend initial enrollment meetings was carried out in June, 2004. About 280 subjects were re-invited to participate in the study; 100 women attended enrollment meetings and about 70 of them were enrolled in the study. During this second phase, we used 30 social workers from local public health offices to assist in contacting and locating subjects. The overall rate of attendance at enrollment meetings among potential subjects was more than 50%, and the rate of enrollment among eligible subjects was more than 85%. After this first pilot phase, we introduced some changes into recruitment strategies, including more flexibility in recruitment timelines, adding more social workers, and increasing the number of attempts of contacting subjects prior to enrollment meetings. We also developed a practical step by step recruitment decision tree to accommodate most recruitment scenarios. In November 2004, a third phase of recruitment was conducted in areas outside Bauru, targeting about 1,100 subjects and 285 were enrolled.

As of November 30, 2006, about 355 subjects are actively participating at the Bauru site and taking folic acid pills. To date, there have been 62 pregnancies in the Bauru sample; 3 resulting in miscarriages, 49 delivered and 9 are ongoing.

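### The historical-control comparison assumes no major event affecting recurrence, yet the same article reports mandatory folic acid flour fortification in Brazil from June 2004

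*Protocol article*

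**What the plan says.** The protocol article, Secondary hypotheses, includes "A decrease in recurrence of NSCL/P in the group of study subjects compared to an historical control group" drawn from the participating craniofacial clinics. A second historical hypothesis expects a larger decrease against that group in the 4 mg arm than in the 0.4 mg arm.

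The section Historical control group explains that a placebo was ruled out on ethical grounds. The comparison is meant to show the effect of folic acid between 0.4 and 4 mg against women not taking the 0.4 mg daily dose, and each arm may also be set against the same controls. On internal validity it says that "no major historical events that could affect recurrence rates of NSCL/P in this population are expected to have occurred" in the years just before the study. It adds that rates over a long period will show any changes over time, and that differences between the two arms' decreases can be attributed to the folic acid given. It states no calendar window for the historical births and does not mention fortification.

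The Background section Folic acid fortification and oral clefts states: "In Brazil, fortification of wheat and corn flour with folic acid became mandatory in June 2004". It gives the level ("Flour is fortified at a dose of 150 μg/100 g") and a consumption assumption ("Assuming that women consume about 200 g of fortified flour on average per day"), and concludes that intake should rise by about 300 µg a day.

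On timing, the section on the initial pilot says that "study enrollment was initiated in Bauru in January 2004". Porto Alegre followed in May 2005 and Salvador in December 2005. The note to Table 10 has new enrolment running to March 2011.

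**The concern.** A historical comparison needs the background exposure of the two groups to be similar, or a way to allow for the difference. Here the event that may separate them is nationwide exposure to the substance under test. If historical births conceived before June 2004 are used, a lower recurrence among study births could come from the pills, the flour or both, and no analysis of those two groups alone can tell them apart.

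The article makes a related criticism in its own Background, where it faults studies of prevalence over time for confounding by other factors that change simultaneously. At stake is the secondary conclusion that supplementation at 0.4 mg or more lowers recurrence compared with no such dose. This is the only planned comparison that speaks to folic acid against women not taking that dose.

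**Working it through.** **1. The article's intake figure.** Inputs from Folic acid fortification and oral clefts: 150 µg per 100 g of flour and 200 g a day.

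150/100 × 200 = 300 µg/day, which reproduces the stated figure.

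**2. Size against the study doses.**
- Share of the 0.4 mg dose: 300/400 = 75%.
- Share of the 4 mg dose: 300/4000 = 7.5%.
- Share of the mean dose in the total sample, assuming equal arms: (0.4 + 4)/2 = 2.2 mg, and 300/2200 ≈ 14%.
- Share of the added intake relative to unfortified controls: 300/(300 + 400) = 43% in the 0.4 mg arm and 300/(300 + 4000) = 7% in the 4 mg arm.

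**3. How many study births could precede fortification.** The first Bauru phase enrolled 134 women. Allowing all of them the full five months from January to June 2004, at the article's 0.0957 births per subject-year:

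134 × 5/12 × 0.0957 ≈ 5 births; 5/1582 ≈ 0.3% of the target.

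Even if all 50 births already observed (Sample size) were unexposed, 50/1582 ≈ 3%. Almost all study births are therefore conceived under mandatory fortification. The corresponding share of historical births cannot be computed, because no window is given.

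**4. What the cited prevalence changes would mean.** US falls in CL/P of 3%, 5% and 12% (all described as generally non-significant) on the 5% reference rate from Power analysis:

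5% × 0.03 = 0.15 points; 5% × 0.12 = 0.60 points.

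The primary hypothesis concerns a 2.5-point difference (5% to 2.5%). The same section also reports a slight non-significant increase in oral clefts in Ontario and no significant change in Chile, so the range must include zero and the opposite sign.

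**5. Illustrative effect on the total-sample-versus-history test.** Assumptions: pre-fortification historical rate 5%; no supplement effect; all historical births unexposed and all 1,582 study births exposed; one-sided two-proportion z-test at 5%; 791 to 20,000 historical births (the article gives no number). With fall r, study rate p = 0.05(1 − r) and difference d = 0.05 − p, the rejection probability is Φ[(d − 1.645·se₀)/se₁], where se₀ is the pooled and se₁ the unpooled standard error.

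Example with r = 12% and 1,582 historical births: d = 0.006, se₀ ≈ 0.00752, se₁ ≈ 0.00752, so Φ(−0.85) ≈ 20%.

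| Assumed fall from fortification | Rejection at nominal 5% |
|---|---|
| 0% | 5% |
| 3% | 7–8% |
| 5% | 9–11% |
| 12% | 17–27% |

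A rise, as in Ontario, would work the other way and hide a true benefit.

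**6. The dose contrast.** Write p₄, p₀.₄ and p_h for the 4 mg, 0.4 mg and historical rates. The difference in relative decreases is (1 − p₄/p_h) − (1 − p₀.₄/p_h) = (p₀.₄ − p₄)/p_h. With no dose effect it is zero whatever p_h is.

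With a true 50% dose effect and no fortification effect: (0.05 − 0.025)/0.05 = 50 points. With a 12% fortification effect: (0.044 − 0.022)/0.05 = 44 points. The randomised relative reduction is 1 − 0.022/0.044 = 50% in both cases.

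**The case against.** Several points on the other side have force.

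- **Both arms share fortification.** This stands. A reader might infer that both historical hypotheses, or even the trial's dose conclusion, are invalid. The documents do not support that: step 6 shows the arm-to-arm difference keeps its null at zero and is only rescaled by the historical rate.
- **The historical window is undated.** This stands. It is tempting to say that exposure to fortification and membership of the study coincide almost completely, but births after June 2004 are not excluded from the historical group. The window may be set in fuller documents that are not shown.
- **Fortification may not affect clefts.** This stands in part. The article itself suggests that low doses may not prevent even first occurrence, and Chile, with a higher level (220 against 150 µg/100 g), showed no significant change. The sentence is therefore better called overconfident than plainly false. However, the article also says that longer periods may be needed for a full evaluation.
- **Trend data are planned.** This stands only in part. Trends can show a shift in historical rates, but by themselves they cannot separate flour from pills among study births.
- **Literal timing.** June 2004 falls after the January 2004 start, so for the first Bauru enrolees fortification is concurrent rather than preceding. It does precede Porto Alegre, Salvador and the continued phase. Either way it divides study births from earlier ones.

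**Conclusion.** The concern holds in a limited form. The stated premise of the historical comparison conflicts with the article's own account of fortification. The hypothesis on the total sample against history, and the comparisons of a single arm against history, can therefore mix the study supplement with fortified flour.

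Neither the size nor the presence of bias is known. If the US figures carried over from prevalence to recurrence, the apparent benefit would be 0.15 to 0.60 points, and under the assumptions in step 5 false rejection would be about 7% to 27% instead of 5%. The Ontario and Chile results allow for no bias or a reversed one. A reader might infer that the historical conclusion must be wrong even if the plan is followed exactly; the evidence supports only that it could be.

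The primary randomised comparison is not biased. The point should be fixed, but it concerns secondary comparisons only.

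**What to change.** Replace the sentence on historical events with an acknowledgement that fortification became mandatory in June 2004 and may contribute to any difference from historical controls.

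Restrict the historical controls to births conceived after fortification took effect. If there are too few, report historical recurrence separately for conceptions before and after June 2004, and treat the total-sample and single-arm-versus-history comparisons as descriptive, without attributing a difference to the study supplement. Base the conclusion on dose on the randomised 4 mg versus 0.4 mg comparison.

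The cost is a change of wording and the use of birth dates from clinic records. The downside is a smaller historical group or a weaker secondary claim. Whether enough post-fortification births exist cannot be judged from the article.

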#### Pilot studies

##### Initial pilot study and subsequent recruitment at Bauru

With funding from NICHD’s Global Network for Women’s and Children’s Health Research, study enrollment was initiated in Bauru in January 2004. This initial pilot aimed at first recruiting about 500 subjects, identified through the records of the Hospital de Reabilitação de Anomalias Craniofaciais (HRAC) clinic, and located within 100 Km of Bauru, using a field-based strategy for recruitment and follow-up. Letters were mailed to 526 women inviting them to enrollment meetings in local communities; 181 women attended the enrollment meetings, and 134 women were enrolled (96% of those eligible). Several factors contributed to low attendance at these enrollment meetings. We found that 23% of the 500 subjects had either moved out of the catchment area or could not be located and that 12% had had a tubal ligation. The inconvenient recruitment and follow up strategies required multiple visits and poor compliance with these was amplified by poverty.

An extension of this pilot study to re-contact potential subjects from the first sample who did not attend initial enrollment meetings was carried out in June, 2004. About 280 subjects were re-invited to participate in the study; 100 women attended enrollment meetings and about 70 of them were enrolled in the study. During this second phase, we used 30 social workers from local public health offices to assist in contacting and locating subjects. The overall rate of attendance at enrollment meetings among potential subjects was more than 50%, and the rate of enrollment among eligible subjects was more than 85%. After this first pilot phase, we introduced some changes into recruitment strategies, including more flexibility in recruitment timelines, adding more social workers, and increasing the number of attempts of contacting subjects prior to enrollment meetings. We also developed a practical step by step recruitment decision tree to accommodate most recruitment scenarios. In November 2004, a third phase of recruitment was conducted in areas outside Bauru, targeting about 1,100 subjects and 285 were enrolled.

As of November 30, 2006, about 355 subjects are actively participating at the Bauru site and taking folic acid pills. To date, there have been 62 pregnancies in the Bauru sample; 3 resulting in miscarriages, 49 delivered and 9 are ongoing.

##### Revision of subject recruitment/follow-Up strategies and pilot at clinic sites

We identified some limitations in the strategies originally developed to identify, recruit, and follow up subjects at the Bauru site.

Inaccurate and outdated contact information with high population mobility decreased the number of available cases. 18% of potential subjects were untraceable.

Inviting subjects to attend prescheduled meetings for screening and enrollment lowered subject motivation to participate due to extra effort on their behalf, further intensified by the high prevalence of poverty in the targeted population.

The follow-up strategy also seemed intensive and burdensome by requiring subjects to attend follow-up visits and provide blood samples on a bimonthly basis, without providing any real direct incentives (besides potential benefits of the study pills). This also lowered compliance with the follow up schedule.

It became clear that the required sample size could not be secured through the Bauru site alone.

In order to address these limitations, we developed new sampling, recruitment, and follow up strategies using a clinic model. This strategy focuses on women who still attend the clinic for their own craniofacial care or for their children’s care, but can also include women who no longer attend the clinic regularly. We identified six new clinics in Brazil as candidates to join the study and pilot test these new strategies. Three of these clinics, Hospital de Clinicas de Porto Alegre (HCPA) in Porto Alegre, Hospital Santo Antônio- Centrinho-Obras Sociais Irmã Dulce (OSID) in Salvador, and Instituto Materno Infantil [name]/IMIP (IMIP) in Recife formally joined the study. HCPA and OSID were able to start the pilot test studies. Recife was put on hold until additional funding could be secured.

The new recruitment strategies implemented at Porto Alegre and Salvador involve identifying potential subjects from subjects who attend the clinic for care. Registered subjects who are not scheduled to visit the clinic may still be invited by phone or mail to participate in the study. Initial screening and enrollment procedures occur as soon as a subject agrees to participate, often during first contact with subject, eliminating the need for extra visits for enrollment. Study pills are sent every two months to subjects by mail and health and pregnancy checkups are conducted mostly through phone rather than in person. In-person follow-ups are currently limited to the first two months after enrollment, to measure post supplementation folate and B12 levels, and every six months thereafter or at pregnancy. These procedures will be further eased in the proposed continuation. Food vouchers are being provided at enrollment and at every third completed follow-up.

This clinic-based strategy is expected to ensure a continuous increase in the number of study subjects and to enhance efficiency. Inaccuracies of contact information inherent in clinical registries can be avoided by this approach using in person contact. Further, the groups of subjects recruited through this approach may be more motivated to participate in prevention research given that the majority are still obtaining treatment either for themselves or their children and may thus perceive a higher burden of CL/P compared to groups with completed treatments. Reducing the frequency of blood collection and of in-person attendance by mailing pills and conducting follow up by phone also make subjects more willing to maintain active participation after enrollment. These strategies also require fewer personnel since most activities can be implemented at the clinic’s research unit by the clinical coordinators.

Subject recruitment began in May 2005 at Porto Alegre site. Through November 30 2006, 137 women have been screened and 103 enrolled. Recruitment activities began in Salvador in December 2005. Through November 30, 2006, 174 women have been screened and 106 enrolled. Recruitment and follow-up strategies have been successful with no significant problems. Mailing the pills and conducting follow-ups by telephone proved easy and effective.

